### Sample size

This study focuses on MRI data. The sample size was calculated based on similar previous studies. Through reading the research literature on the mechanism of the functional effects of acupuncture on the brain, we found that the acute phase of stroke is generally characterized by an acute condition and poor compliance. Desmond et al. (8) showed that when analyzing functional MRI data with a free threshold of 0.05, it is probably necessary to include at least 12 subjects to achieve an activation efficacy of 80% or more at the single voxel level. Anecdotal evidence (9) suggests that fMRI studies typically involve 12 to 16 subjects per group. Therefore, we included 16 subjects in each group. Considering the high dropout rate, we set the 20% dropout rate and finally included 20 subjects per group. So, a total of 40 CIS patients and 20 healthy people will be enrolled.

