### Secondary outcomes

National Institutes of Health Stroke Scale (NIHSS), modified Rankin Scale (mRS), Fugl–Meyer Assessment (FMA), Modified Barthel Index (MBI) and EuroQol Five Dimensions Questionnaire (EQ-5D) will be assessed before and after 2 weeks of treatment as secondary outcomes.

FMA (16) is widely used in motor function assessment which can reflect the level of limb function recovery in patients with post-stroke disability. The scale focuses on limb joint flexibility and muscle strength, including 66 points for the upper limbs and 34 points for the lower limbs, with a total score of 100 as normal. Currently, the Spanish, Russian, and German versions of the FMA are used for clinical assessment with high sensitivity and validity. Consistency of motor scores in patients with post-stroke dysfunction due to harmonization of kinematic measurement tools (17).

NIHSS (18) can quickly measure the severity of stroke and is recommended as a valid tool for stroke in the emergency department. It consists of 15 items with a total score of 42, the higher the score, the more severe it is. Numerous data demonstrate its reliability, validity, ability to predict stroke outcomes, and strong correlation with infarct foci on imaging. The NIHSS only provides a cursory assessment of the patient’s impairment and does not provide detailed information.

The mRS (19) is highly reproducible and has convergence with other disability scales. Compared to the Barthel Index, mRS is reliable in that it predicts outcomes more accurately. The World Health Organization (WHO) (20) recommends the mRS as an indicator of stroke outcome. The mRS is categorized into 7 grades covering physical function and ability to live, allowing for assessment of patient prognosis.

The MBI is a 100-point scale that assesses 10 essential abilities of patients in their daily lives, and is one of the more widely used and researched methods of assessing activities of daily living. EQ-5D has five dimensions to measure health, including mobility, self-care, daily activities, pain/discomfort, and anxiety/depression. EQ-5D-5L (21) scale which each dimension is divided into five levels, increasing the reliability, validity, and sensitivity of the measurement tool.

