### Data collection and statistical analysis

Data will be collected using the paper CRFs which will be kept in a locked cabinet at the end of the trial. Statistical analysis of data will be performed by an independent researcher. For dislocated subjects, we will record the number and reason for termination, especially adverse events. Data will be analyzed using the R software version R-4.2.2. Statistical significance is defined as a *p* value of <0.05.

For comparisons of baseline material, measurements that follow a normal distribution overall will be expressed as mean ± standard deviation (
$\bar{X}$
 ± SD), and the whole data that do not follow a normal distribution will be expressed as median (interquartile range, IQR) [M (P25-P75)]. Count data will be expressed as the number of cases (n) and percentage (%) using the X^2^ test. The *t*-test or Mann–Whitney U-test will be chosen to compare the two groups’ scores on each scale based on a normal distribution and homogeneous variance. For within-group comparisons, changes in scores will be assessed by paired *t*-test or Wilcoxon rank-sum test. For subjects who discontinued or deviated from the intervention, listwise deletion or multiple interpolation will be used.

The multimodal MRI images will be analyzed by MATLAB 2023a and the statistical parameter graph software Statistical Parametric Mapping (SPM)12. Before data processing, all data will be removed the first 10 time points to retain the stabilized images; and adjust for differences arising from the time points, after which orientation alignment will be performed; and all aligned functional images will be aligned to the montreal neurological institute (MNI) space with a voxel standard size of 3 mm × 3 mm × 3 mm, and then the functional images will be smoothed with a Gaussian kernel of 6 mm × 6 mm × 6 mm. Afterward, the images will be datamined by extracting the indicators. Data will be analyzed with two independent samples *t*-tests to compare the differences between the patient group before treatment and the healthy group, as well as the differences between the acupuncture group and the no-acupuncture group after treatment. The longitudinal changes in MRI indexes before and after the respective treatments of the two groups of patients will be observed with paired *t*-tests. Age, gender, BMI, blood pressure, and history of diabetes will be used as covariates in data analysis.

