Finally, the statistically significant MRI index values of the acupuncture group will be extracted and analyzed by Pearson correlation with the clinical scores of this group before and after treatment.

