In this trial, we will study the brain mechanisms produced by the main point of XNKQ acupuncture in cerebral infarction patients. The XNKQ acupuncture method produces therapeutic effects by stimulating the combination of three acupoints: Neiguan (PC6), Shuigou (DU26), and Sanyinjiao (SP6). It has been widely used in the rehabilitation of stroke patients and has shown remarkable effects. In a meta-analysis of 12 randomized controlled studies of acute stroke, Yang et al. (28) found that XNKQ acupuncture significantly reduced the disability rate and improved the clinical efficacy and quality of life. In another systematic review (29), they analyzed the long-term efficacy of XNKQ and found reduced recurrence, disability, and mortality rates. Scholars also have conducted a lot of basic research (30) on acupuncture to explain the mechanism of XNKQ acupuncture. However, its brain mechanisms remain unknown. Till Nierhaus et al. (31) studied healthy individuals using the combination of PC6-DU26-SP6 and found that this combination could have an effect on functional connectivity in motor areas minutes after acupuncture. They also found that the point location only has an impact when the acupuncture points are stimulated. Based on this, we investigate the sustained effect of this combination of acupoints in stroke patients with motor dysfunction.

Zhang et al. (5) concluded that in terms of experimental design, previous research commonly used fMRI, while in terms of analytical indicators, ALFF, ReHo, and FC were more commonly used In our experiments, we will use multimodal MRI techniques to analyze brain function, also focusing on gray matter, white matter fiber tracts, and cerebral blood flow perfusion. Finally, in order to explore the predictive power of the above indexes for patient prognosis, we will evaluate the correlation of brain indicators with the clinical symptom indexes.

In summary, the results of this study will be expected to provide an argument for the mechanism of the action of XNKQ. Exploring its central mechanisms with multimodal MRI can provide an evidence-based basis for future clinical promotion.

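### The brain–score correlation uses the acupuncture arm alone, so it cannot separate acupuncture from ordinary recovery, and it is too imprecise and unspecified for the prognosis wording

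*Protocol article*

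**What the plan says.** The final sentence of *Data collection and statistical analysis* sets the arm and the selection: "the statistically significant MRI index values of the acupuncture group will be extracted". It goes on to set the coefficient and the scores, so that these values are to be "analyzed by Pearson correlation with the clinical scores of this group before and after treatment".

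The Discussion gives the purpose: "in order to explore the predictive power of the above indexes for patient prognosis, we will evaluate the correlation of brain indicators" with clinical indexes.

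Four other places bear on this:

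- *Outcome measures* and Table 1: both patient groups are assessed at baseline and week 2, and Table 1 lists imaging and all five scales (FMA, NIHSS, mRS, MBI, EQ-5D) at both times. No later assessment is listed.
- *Data collection and statistical analysis*, earlier in the section: between-group tests of the scales are a t-test or a Mann–Whitney test, depending on distribution. The significance threshold is given as "Statistical significance is defined as a *p* value of <0.05".
- *Secondary outcomes*: "The mRS is categorized into 7 grades covering physical function and ability to live".
- *Sample size*: "Therefore, we included 16 subjects in each group", and then "we set the 20% dropout rate and finally included 20 subjects per group".

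**The concern.** The trial is meant to explain how acupuncture acts on the brain. Patients enter within two weeks of a first stroke, when some improvement without acupuncture is to be expected. If an MRI index and a motor score move together in treated patients, the same link might be present in untreated patients. Only the control arm can show that, and this analysis leaves it out although its data are collected.

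The wording of the purpose adds a second problem. Prognosis implies that an early measurement is related to a later outcome. The analysis sentence names no such model, and the latest outcome is the week-2 score.

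At stake is a set of correlations from 16 to 20 patients that could be published as evidence of mechanism or prognostic value when they can establish neither.

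**Working it through.** **Inputs.** Completers per arm 16, enrolled per arm 20, dropout 20% (*Sample size*). Alpha 0.05 (*Data collection and statistical analysis*); two-sided is assumed because the article does not say. The 80% power level is used as a yardstick; the article sets no power or effect size for the correlation.

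**The plan's own figure.** 16 / (1 − 0.20) = 20 per arm, as stated. The available n is therefore 16 to 20 in one arm, or 32 to 40 in both.

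**Formulas.**
- Critical |r| = t / √(n − 2 + t²), with t the 97.5% point on n − 2 degrees of freedom.
- Detectable |r| at 80% power = tanh[(1.960 + 0.842) / √(n − 3)].
- Power for true r = Φ[atanh(r)·√(n − 3) − 1.960].

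For n = 16: 2.802 / √13 = 0.777, and tanh(0.777) = 0.65. For n = 32: 2.802 / √29 = 0.520, and tanh(0.520) = 0.48.

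| Patients analysed | Critical \|r\| | Detectable \|r\|, 80% power | Power if r = 0.5 |
|---|---|---|---|
| Acupuncture arm, 16 | 0.50 | 0.65 | 51% |
| Acupuncture arm, 20 | 0.44 | 0.59 | 62% |
| Both arms, 32 | 0.35 | 0.48 | 84% |
| Both arms, 40 | 0.31 | 0.43 | 92% |

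An observed r of 0.5 has a 95% interval of tanh(0.549 ± 1.96/√13) = 0.01 to 0.80 at n = 16. At n = 32 it is tanh(0.549 ± 1.96/√29) = 0.18 to 0.72.

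**Cost of adjustment.** Each covariate takes about one from n − 3. With arm and baseline score in the model, n = 32 gives tanh(2.802/√27) = 0.49 and n = 40 gives tanh(2.802/√35) = 0.44. Most of the gain remains.

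**What the gain does not cover.** The both-arms rows apply to an association common to the arms. As a guide to the interaction, comparing two independent correlations with 16 patients each has standard error √(2/13) = 0.392 on the Fisher scale. The detectable difference is 2.802 × 0.392 = 1.10, for example r = 0.80 in one arm and 0 in the other. With 20 each it is 2.802 × √(2/17) = 0.96, for example 0.74 against 0. Specificity to acupuncture can therefore be estimated, but only large contrasts would be detected.

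**Purpose against method.** The Discussion speaks of prognosis. The analysis sentence does not say whether the MRI value is baseline, post-treatment or change, or which score it is paired with. The assessment schedule ends at week 2. Prognosis can thus mean at most a two-week score, and no baseline-to-later analysis is committed to.

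**Pearson against the distribution rule.** The same scales get a rank test when they are not normal in the group comparison, but Pearson unconditionally in the correlation.

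**The case against.** The strongest defence is that this is a closing exploratory step, neither a primary nor a listed secondary outcome. The Discussion says only that predictive power will be explored, and a one-arm correlation can explore a prognostic association, if imprecisely. An article may also leave details of pairing and coefficients to a fuller document. This stands in part: it rules out saying that the analysis cannot serve its aim at all. It does not answer the restriction to one arm, which the article states outright.

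A reader might infer four stronger faults that the text does not support.

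- *Selecting significant MRI values makes the correlation circular.* Selection is on a mean difference, and the correlation is with a separate clinical score. In a simulation with n = 16, no true association and selection by paired t-test (200,000 runs), the false-positive rate for change or post-treatment correlations stayed at 4.9% to 5.1%.
- *The two visits are pooled as 32 independent points.* Pooling would inflate false positives, but the article does not say it will be done. Separate correlations at each visit fit the wording equally well.
- *The correlation is only between same-time values.* Baseline MRI against week-2 score also fits the wording. The supportable criticism is that no pairing is fixed.
- *Pearson is invalid because the scales are ordinal.* Only the mRS is described as grades; FMA, NIHSS and MBI are summed scores. In simulation at n = 16, Pearson on a graded score kept about a 5% error rate, and at a latent r of 0.5 on a six-level score it had 49% power against 45% for Spearman. The fault is inconsistency with the section's own rule.

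A count of expected false positives would need the number of tests, which the article does not give.

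**Conclusion.** The point holds in this form: the correlation leaves out half of the randomised patients, cannot distinguish an acupuncture-specific association from ordinary recovery, and needs a true |r| of about 0.65 (n = 16) or 0.59 (n = 20) for 80% power. Both arms together lower this to about 0.48 or 0.43 for a common association. The prognosis wording goes beyond an analysis with no named predictive model and no outcome after week 2. The fixed choice of Pearson is a minor inconsistency with little numerical effect.

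The figures assume a two-sided 5% test, the Fisher approximation and no multiplicity adjustment. That early recovery is a plausible rival explanation follows from enrolment within two weeks of onset; the article gives no figure for it. Because the analysis is exploratory, this should be corrected before analysis but does not threaten the randomised comparison.

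**What to change.** Replace the final sentence of *Data collection and statistical analysis* with an analysis of all randomised patients:

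1. **Mechanism.** Relate change in the MRI index to change in the score, with arm and arm-by-change terms. Report the interaction with its confidence interval, whatever its p value.
2. **Exploratory prognostic question.** Regress the week-2 score on the baseline MRI index, adjusted for baseline score and arm.
3. **Visits.** Do not treat a patient's two visits as independent observations.
4. **Method.** Apply the section's existing distribution rule to these analyses, with a rank or ordinal method for the mRS.
5. **Wording.** Describe the results as hypothesis-generating associations with the two-week score. If the one-arm correlation is kept, delete the Discussion's phrase "in order to explore the predictive power of the above indexes for patient prognosis".

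The cost is a few sentences and a little programming. No new visit, scan or patient is needed, because the control-arm data are already scheduled.

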### Trial status

The trial will begin recruitment and treatment on 7 December 2023, and is expected to be completed by 30 December 2025.

### Quality control

In order to implement the project smoothly, we will rigorously standardize the intervention and evaluation processes. Acupuncturists with more than five years of experience will be familiar with the conduct of intervention and control group interventions to ensure consistency in the study. The assessors will be uniformly trained on the scales to ensure the reliability of the data. Ethics committee members will also review implementation throughout the trial.

## Discussion

Due to the specificity of the intervention, we were unable to achieve a double-blind design. Therefore, we design a single-blind, randomized controlled trial to evaluate the brain mechanism of the acupuncture group in the treatment of limb dysfunction in comparison to the non-acupuncture group. Patients who meet the inclusion criteria will be enrolled and randomly assigned to either the XNKQ group or the control group. Indicator assessors who are not aware of the subgroups will be objective in making indicator evaluations to avoid bias.

The fMRI is widely used in the study of brain mechanisms of acupuncture therapy for stroke. Past studies of cerebral mechanisms in patients with cerebral infarction, were focused on single acupoint such as Zusanli (ST36) and Yanglingquan (GB34). Zou et al. (22–24) studied GB34 and found that this acupoint can activate multiple sensory and motor imagery areas in patients. The FC between bilateral M1 was decreased in patients with cerebral infarction and increased after acupuncture on GB34. The researchers also found that patients tended to have increased needling effects early in the stroke period (within 1 month) and decreased responses thereafter (1–3 months). Therefore, it is necessary to intervene acupuncture treatment as soon as possible. ST36 (25) has been shown to improve post-stroke motor deficits by activating the primary motor cortex and somatosensory-motor areas. In another randomized controlled trial, ST36 (26) also increased the compensatory function of the lateral circulation in the brains of stroke patients. In addition, researchers have studied the combination of multiple acupoints and found that the combination of Baihui-Yintang-Neiguan (27) improves cerebral blood perfusion in post-stroke patients.

In this trial, we will study the brain mechanisms produced by the main point of XNKQ acupuncture in cerebral infarction patients. The XNKQ acupuncture method produces therapeutic effects by stimulating the combination of three acupoints: Neiguan (PC6), Shuigou (DU26), and Sanyinjiao (SP6). It has been widely used in the rehabilitation of stroke patients and has shown remarkable effects. In a meta-analysis of 12 randomized controlled studies of acute stroke, Yang et al. (28) found that XNKQ acupuncture significantly reduced the disability rate and improved the clinical efficacy and quality of life. In another systematic review (29), they analyzed the long-term efficacy of XNKQ and found reduced recurrence, disability, and mortality rates. Scholars also have conducted a lot of basic research (30) on acupuncture to explain the mechanism of XNKQ acupuncture. However, its brain mechanisms remain unknown. Till Nierhaus et al. (31) studied healthy individuals using the combination of PC6-DU26-SP6 and found that this combination could have an effect on functional connectivity in motor areas minutes after acupuncture. They also found that the point location only has an impact when the acupuncture points are stimulated. Based on this, we investigate the sustained effect of this combination of acupoints in stroke patients with motor dysfunction.

Zhang et al. (5) concluded that in terms of experimental design, previous research commonly used fMRI, while in terms of analytical indicators, ALFF, ReHo, and FC were more commonly used In our experiments, we will use multimodal MRI techniques to analyze brain function, also focusing on gray matter, white matter fiber tracts, and cerebral blood flow perfusion. Finally, in order to explore the predictive power of the above indexes for patient prognosis, we will evaluate the correlation of brain indicators with the clinical symptom indexes.

In summary, the results of this study will be expected to provide an argument for the mechanism of the action of XNKQ. Exploring its central mechanisms with multimodal MRI can provide an evidence-based basis for future clinical promotion.

## Ethics statement

The study involving human subjects was reviewed and approved by the Ethics Committee of IRB of The First Teaching Hospital of Tianjin University of TCM (TYLL2023[K]031). This study complied with the Declaration of Helsinki. Written informed consent about this study was provided by the participants. The investigators will report any changes of protocol or informed consent to the Ethics Committee and Registry.
